## Abstract

**Background:**

The prevalence of fibromyalgia increases worldwide and is characterized by widespread and chronic pain. Treatment is difficult and includes both drug and non-drug approaches. Milnacipran, an antidepressant, is used for fibromyalgia, with a possible beneficial effect on central pain modulation. Our hypothesis is that the efficacy of milnacipran in fibromyalgia depends on the performance of pain inhibitory controls.

**Methods/design:**

A randomized, double blind, clinical trial (NCT01747044) with two parallel groups, in 48 women with fibromyalgia, is planned in the Clinical Pharmacology Center, University Hospital, Clermont-Ferrand, France. Conditioned pain modulation (estimated with thermal stimuli using a numeric pain rating scale), the primary endpoint measure, is evaluated before and one month after treatment with milnacipran or placebo. Secondary outcome measures include the predictability of pain descending pathways performance for milnacipran efficacy, tolerance and cognitive function. Data analysis is performed using mixed models; the tests are two-sided, with a type I error set at alpha = 0.05. Not only will this trial allow estimation of the beneficial effect of milnacipran on pain and on descending pain pathways but it will also evaluate whether the performance of this modulatory system could be predictive of its efficacy in alleviating pain.

**Discussion:**

This method would allow clinicians to take a pro-active attitude by performing a rapid psychophysical test before starting milnacipran treatment and would avoid unnecessary prescription while preventing therapeutic failure in patients who often face this recurrent problem.

**Trial registration:**

ClinicalTrials.gov NCT01747044.

## Background

Fibromyalgia has a prevalence estimated at 2 to 5% of the general population in Europe [1] and in the United States of America [2] and is approximately seven times more common in women than in men [3]. Diagnostic criteria have been validated since 1990 by the American College of Rheumatology and have been enlarged in the 2010 revision to consider not only tender points but also cognitive problems and the extent of somatic symptoms [4]. The pathophysiology of fibromyalgia is uncertain but a dysfunction of descending pain inhibitory pathways [5-7] has been described as a cause or a consequence of the pathology [8]. These pathways originate in the brainstem and are involved in diffuse noxious inhibitory controls (DNICs) that are part of a central pain modulatory system relying on spinal and supraspinal mechanisms [9]. This pain modulatory system can be easily triggered and studied in experimental settings [10,11] using the conditioned pain modulation test, where the administration of two simultaneous painful stimuli typically results in pain inhibition [12,13]. Stimulation of DNICs is commonly used to evaluate any impairment of descending pain modulation.

Antidepressants have a mechanism of action that involves a number of neuromediators (serotonin, noradrenaline) within the brain-brainstem-spinal-cord axis and affects pain descending pathways [14]. Duloxetine and milnacipran are serotonin and norepinephrine reuptake inhibitors and have been approved for treatment of fibromyalgia by the Food and Drug Administration [15-17] for their analgesic properties [14]. Experiments on the safety, tolerability, and clinical benefits of long-term milnacipran use in patients with fibromyalgia have shown good results [18]. A review of four double blind studies focused on the efficacy of milnacipran in fibromyalgia [18]: a substantial improvement on global status was observed and more than 30% pain relief was obtained but only in 40% patients.

Considering this large variability in response to milnacipran, it is expected that a number of patients will have no alleviation of pain: it would be beneficial for the patient to be able to predict the efficacy of milnacipran in pain associated with fibromyalgia before the prescription of the drug. It would also be important to evaluate cognitive function, which is frequently impaired in chronic pain [19]. This information would enable prescription of the drug to be avoided if no efficacy is expected, and would avoid therapeutic failure in patients who often stop their treatment because of lack of efficacy. Such a predictive approach has been performed with duloxetine in another pathology, painful diabetic neuropathy [13], where the authors have shown that pain alleviation may be predicted from pre-treatment conditioned pain modulation. Such an approach is quite interesting in the context of milnacipran as DNICs are involved in the mechanism of action of both drugs [12,17]. In this trial, we set the mechanistic hypothesis that (1) milnacipran restores the function of descending inhibitory pathways and concomitantly decreases the pain experience in fibromyalgia patients, and (2) this efficacy could be predicted from the performance, before treatment, of pain descending pathways when activated by conditioned pain modulation.

## Methods/design

This study is a prospective, randomized, controlled, double blind clinical trial of two parallel groups, milnacipran versus placebo, in 48 fibromyalgia patients. It is carried out in the Pain Clinic and Clinical Pharmacology Center, University Hospital, Clermont-Ferrand, France. The research ethics committee (Comité de Protection des Personnes Sud-Est 6) gave its approval on October, 18, 2012 (institutional review board number 00008526/AU987), and the Agence Nationale de Sécurité du Médicament et des Produits de Santé on September, 25, 2012, and this trial is registered in ClinicalTrials.gov (trial number NCT01747044).

Patients come twice to the Pain Clinic and Clinical Pharmacology Center, for inclusion and randomization and 1 month later for reassessment.

Eligibility criteria are verified with a complete clinical exam, matching the American College of Rheumatology’s definition of fibromyalgia. Patients meeting the inclusion criteria sign a consent form after receiving oral and written information about the study. At baseline, pain is assessed by a numeric pain rating scale and patients undergo psychophysical and cognitive ability tests. Patients are then randomly assigned to milnacipran (n = 24) or placebo (*n* = 24) for one month’s treatment, with the following titration: 50 mg on the first three days, 75 mg from day 4 to day 6 and 100 mg from day 7 to 1 month. Evaluations and tests are then repeated 1 month later at visit 2. To maintain good compliance and to verify adverse events, patients are telephoned once a week by a clinical research assistant until visit 2.

### Objectives

The primary objective of this trial is to assess whether milnacipran has an influence on DNIC status, by measuring if there is a difference between the results of the conditioned pain modulation test in milnacipran and placebo groups.

The secondary objectives are to assess:Whether the DNIC status could be predictive of milnacipran efficacy in fibromyalgia,The evolution of pain threshold with milnacipran,The impact of milnacipran on cognitive parameters; comprehension tests, executive function, memory, attention and decision making,Tolerance towards milnacipran.

### Participants and setting

#### Inclusion criteria

Patients are eligible for this study if they are over 18 years old with a confirmed diagnosis of fibromyalgia, are able to understand and willing to follow the study protocol and have given informed consent.

#### Exclusion criteria

Patients will not be accepted if there is contra-indication of milnacipran treatment, if they have hypertension or heart disease, known renal impairment, a medical or surgical history incompatible with the study, or a psychiatric disorder, or if they have shown signs of suicidal behavior or significant suicidal ideas. This study also excludes patients with diabetes, patients with acute and chronic intoxication with alcohol, hypnotics, analgesics, or opioids, patients taking diuretics or a treatment inducing hyponatremia, patients taking non-steroidal anti-inflammatory drugs, oral anticoagulants, aspirin or other drugs that are likely to induce bleeding, and patients taking drugs with serotonin and noradrenaline reuptake inhibition, digitalis, cytochrome P450 1A2 inhibitors, or 5-hydroxytryptamine serotonin receptor agonist. Women of childbearing age not using an effective contraceptive will be excluded, as will pregnant or breastfeeding women, patients taking part in another interventional trial or patients unable to understand the patient information and the informed consent form.

### Eligibility and randomization

Patients are recruited during their admission to the Pain Clinic and Clinical Pharmacology Center. Before enrolment, informed consent is obtained from each patient in the presence of the investigator. Randomization will be conducted to balance group sizes according to a computer-generated allocation sequence by blocks with Stata software by a statistician independent of the protocol [20]. The randomization sequence is generated using random blocks and the size of the blocks is unknown, to avoid guessing during the trial. Subjects are then randomized to milnacipran or placebo groups. Double blinding will be fully respected with the patients and the members of staff. A research nurse who is only involved in drug allocation will be in charge of drug administration. Treatments are prepared in the Central Pharmacy of the University Hospital with double blinding according to Good Pharmaceutical Practice. The milnacipran and placebo will be administered in the form of white capsules that look alike.

### Definition of outcome measures

#### Primary outcome measure

The primary outcome measure is the change of conditioned pain modulation effect induced by milnacipran compared with placebo.

#### Secondary outcome measures

Secondary outcome measures are the assessment of the evolution of pain threshold, DNIC status, milnacipran efficacy and tolerance, and cognitive status.

The summary of the different evaluations and tests is reported in Table 1.

**Table 1 Tab1:** **Summary of evaluation for a patient**

**Study visit**	**Visit 1**	**Phone call**	**Visit 2**
	**Day 0**	**Day 0 + 7 days, 14 days, 21 days (interval 1 day)**	**Day 28**
***Clinical interviews***			
Informed consent	×		
Inclusion and exclusion criteria	×		
Clinical examination: diagnosis of fibromyalgia	×		
***Measures***			
Numeric pain rating scale	×		×
Assessment of pain threshold to a thermal stimulus	×		×
Test-stimulus intensity ‘pain 60/stimulus’	×		×
Conditioned pain modulation test	×		×
Cantab® tests	×		×
***Treatment***			
Randomization: delivery of therapeutic units	×		
Reporting of adverse events and concomitant treatments	×	×	×
Treatment compliance		×	×
Reporting of adverse events and concomitant treatments	×	×	×
Return of therapeutic units			×

### Conditioned pain modulation

Conditioned pain modulation is evaluated before treatment randomization (visit 1, CPMv1) and after 1 month treatment (visit 3, CPMv3). The milnacipran and placebo differences (CPMv3 − CPMv1) are then compared. With pain intensity rated by the patient on a numeric scale from 0 (no pain) to 100 (worst pain possible), the conditioned pain modulation is obtained with the following experiment. An Advanced Thermal Stimulator thermode (Medoc Ltd, Ramat Yishai, Israel) is applied to the volar side of the patient’s dominant forearm. The Medoc PATHWAY system delivers stimulation at the predetermined pain threshold for 10 seconds and the patient rates her pain using the numeric scale. Then the Medoc PATHWAY system delivers a stimulus at the same temperature for 30 seconds and the patient rates her pain using the numerical scale. After the end of these two stimuli (15 minutes), the patient puts the non-dominant hand into a water bath at 46.5°C for 60 seconds. After having dried her hand, the patient has a similar sequence of stimuli for 10 and 30 seconds with pain evaluation using the numeric pain rating scale. The aim of this test is to trigger the stimulation of pain descending pathways. If these pathways are functional, the second series of stimuli will be less painful than the first one because of the inhibitory effect on pain stimuli. It is the reverse if these pathways are not functional, as described in a number of chronic pain situations including fibromyalgia [11,21]. The amplitude of the conditioned pain modulation is given by the difference between the pain scores on the numeric pain rating scale before and after the immersion of the non-dominant hand.

### Assessment of pain thresholds with a thermal stimulus

The Advanced Thermal Stimulator thermode (30 × 30 mm) connected to the Medoc PATHWAY system is applied to the volar side of the patient’s dominant forearm. From the baseline value of 32°C, the Medoc PATHWAY system delivers an adjustable temperature peak (in cold and heat, depending on a regular increase of 1°C increments) and is controlled by rapid feedback. This device is used to evaluate the pain threshold to heat and cold by calculating the mean of three measures. This technique was recently used successfully in neurophysiology studies in human beings [11] and showed similar results to those obtained with a laser [22].

### Test-stimulus intensity ‘pain 60/stimulus’

The Advanced Thermal Stimulator thermode is applied to the volar side of the patient’s dominant forearm. From the baseline value of 32°C, the PATHWAY system delivers a series of peaks starting at 1°C above the pain threshold. Then the temperature increases by 1°C until the patient rates the pain intensity as equivalent to 6/10 on the numeric pain rating scale.

### Cognitive tests

The Cambridge Neuropsychological Test Automated Battery (Cantab®, Cambridge, UK) [19] is a battery of 22 neuropsychological tests, administered to subjects using a touch screen computer and a press-pad. The tests selected are: Motor Screening Test, Stockings of Cambridge, Reaction Time, Cambridge Gambling Task, and Graded Naming Test.

### Data handling and record keeping

All original records, such as consent forms and case report forms, will be archived at the trial site for 15 years. The database file will be anonymized and will also be maintained for 15 years.

### Sample size calculation

According to our previous work and a study of the literature [13], we calculate that a sample size of *n* = 24 patients per randomized group would provide 90% statistical power of detecting an absolute difference of 15 points in the primary outcome, that is, the conditioned pain modulation difference between milnacipran and placebo (with a standard deviation of conditioned pain modulation variation equal to 16 points), at a two-sided alpha level of 0.05. A total of 48 patients will be included.

### Statistical analysis

Statistical analysis will be conducted on an intention-to-treat principle using Stata software, version 13 (StataCorp, College Station, TX, USA). A two-sided *P* value of less than 0.05 will be considered to indicate statistical significance. Baseline characteristics will be presented for each randomized group as the mean ± standard deviation or the median (interquartile range) according to statistical distribution for continuous data, and as the number of patients and associated percentages for categorical parameters. Comparisons between independent groups will be analyzed using the Chi squared or Fisher’s exact test for categorical variables, and by Student’s *t*-test or the Mann–Whitney test for quantitative parameters (notably primary outcome, temporal summation, test-stimulus intensity ‘pain 60/stimulus’, pain rating on the numeric pain rating scale, cognitive parameters, with normality verified by the Shapiro-Wilk test and homoscedasticity by the Fisher-Snedecor test. As suggested by Vickers and Altman [23], the primary analysis will be completed by an analysis of covariance considering conditioned pain modulation at 1 month as a dependent variable, and group and baseline value of conditioned pain modulation as independent parameters. Finally, to study whether the DNICs (assessed using the conditioned pain modulation test) in patients with fibromyalgia would be predictive of milnacipran efficacy, multivariate models such as regression analysis (milnacipran efficacy evaluated by conditioned pain modulation difference taken as a dependant variable [13]) will be performed considering the randomization group and the baseline values of conditioned pain modulation and pain as covariables. Secondarily, a sensitivity analysis concerning missing data will be considered to study their nature (not missing at randomization, missing at randomization and so on) and to propose the most appropriate imputation approach.

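### Secondary outcomes measured at both visits are compared without their baseline values, because the planned ANCOVA covers conditioned pain modulation only

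*Protocol article*

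**What the plan says.** The Statistical analysis section compares groups "by Student’s *t*-test or the Mann–Whitney test for quantitative parameters (notably primary outcome, temporal summation" and continues the list with "test-stimulus intensity ‘pain 60/stimulus’, pain rating on the numeric pain rating scale, cognitive parameters". These tests carry no covariates.

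A baseline-adjusted model follows for the primary outcome: "the primary analysis will be completed by an analysis of covariance considering conditioned pain modulation at 1 month as a dependent variable", with "group and baseline value of conditioned pain modulation as independent parameters". The only other covariate model is the prediction regression, where the outcome is again conditioned pain modulation (CPM): "milnacipran efficacy evaluated by conditioned pain modulation difference taken as a dependant variable".

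Table 1 marks the "Numeric pain rating scale", the thermal pain threshold, the pain 60 stimulus and the Cantab tests at both Day 0 and Day 28. The Methods/design section likewise says that the baseline evaluations are repeated at visit 2.

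The Abstract says that the data are analysed with mixed models. The Statistical analysis section contains no mixed model.

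**The concern.** The authors cite a methodological reference for baseline adjustment, then apply it to one of several outcomes that share the same two-visit structure. For the others, the section names a test with no baseline term and describes no adjusted group comparison.

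These outcomes matter to the trial's claims. The first hypothesis in the Background is that "milnacipran restores the function of descending inhibitory pathways and concomitantly decreases the pain experience in fibromyalgia patients", so the pain rating carries half of it. Pain threshold and cognition are listed secondary objectives.

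With 24 patients per group and no stratification described, chance differences at baseline can be appreciable. A comparison of 1-month values carries part of such a difference into the estimate. A comparison of changes from baseline over-corrects for it. Both are less precise than adjusting for the baseline value already collected.

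**Working it through.** **Inputs.** From the Sample size calculation section: 24 per group, two-sided alpha 0.05, and for the primary outcome a difference of 15, SD 16 and 90% power. The article gives no correlation rho between baseline and 1-month values for any outcome, so rho is an assumption, taken from 0.3 to 0.8. SDs are taken as equal at the two visits.

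**The plan's own figure.** The normal approximation gives n = 2 × (1.960 + 1.282)² × 16² / 15² = 23.9, so 24 per group, with power 90.1%. The stated size reproduces. (The exact t-test gives 88.9% at 24 and passes 90% at 25.) No power is stated for the secondary outcomes.

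**Variance of the group difference**, relative to a t-test on 1-month values:
- t-test on change: 2(1 − rho)
- ANCOVA: 1 − rho²
- so ANCOVA relative to change: (1 − rho²) / [2(1 − rho)] = (1 + rho)/2

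**Power.** By noncentral t with 46 df, the unadjusted test has 80% power for 0.826 SD of the quantity it analyses. ANCOVA power is taken at 0.826 divided by the square root of the variance ratio, with 45 df.

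| rho | Variance ratio vs 1-month value | ANCOVA power where the 1-month t-test has 80% | Variance ratio vs change | ANCOVA power where the change t-test has 80% |
|---|---|---|---|---|
| 0.3 | 0.91 | 84% | 0.65 | 93% |
| 0.5 | 0.75 | 90% | 0.75 | 90% |
| 0.6 | 0.64 | 94% | 0.80 | 88% |
| 0.7 | 0.51 | 98% | 0.85 | 86% |

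Allowing for estimation of the slope (variance inflation 1 + 1/44) lowers each figure by less than one percentage point.

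**Equivalent sample size.** Against the 1-month comparison, 24 per group act like 24/0.75 = 32 at rho 0.5 and 24/0.51 = 47 at rho 0.7.

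**One common effect.** For a true difference of 0.5 SD of the 1-month value (slope inflation included for ANCOVA):

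| rho | 1-month t-test | Change t-test | ANCOVA |
|---|---|---|---|
| 0.3 | 40% | 30% | 42% |
| 0.5 | 40% | 40% | 49% |
| 0.7 | 40% | 59% | 65% |
| 0.8 | 40% | 76% | 80% |

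**Baseline imbalance.** One standard error of the baseline difference is √(2/24) = 0.29 SD. An imbalance of that size shifts the unadjusted 1-month difference by rho × 0.29: 0.14 SD at rho 0.5 and 0.20 SD at rho 0.7. It shifts the change-score difference the other way by (1 − rho) × 0.29: 0.14 SD and 0.09 SD.

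**The case against.** - **The unadjusted tests are valid.** Over randomization they are unbiased and hold their type I error, and the trial claims power only for CPM. This stands. The point concerns precision and conditional imbalance in secondary outcomes, not error control.
- **An article condenses the plan, and the secondary covariates may sit in an unseen document.** This has limited force. The section is not silent: it names the test for these outcomes and says where the ANCOVA applies. It does leave open whether the secondary tests use the 1-month value or the change. Change is defined only for CPM, though the objectives speak of how the pain threshold evolves. ANCOVA has the smaller variance in either case.
- **The Abstract's mixed models could use the baseline.** They could, but the Methods never specify such a model. The two statements need reconciling in any event.
- **The gain is assumed, and rho = 0.5 is where it looks best.** This is partly right. Against the better of the two unadjusted options, the gain is greatest at rho 0.5 and shrinks on either side: from 80% to 84% at rho 0.3, and from 80% to 86% at rho 0.7. The 93% and 98% figures compare ANCOVA with the poorer option at those correlations.
- **Thermal pain threshold is not named in the list.** True, but the list is illustrative and the threshold is a quantitative parameter under the same rule.
- **A linear model may fit skewed Cantab scores poorly.** This is a fair caution. Keeping the Mann–Whitney test as a check largely answers it.

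**Conclusion.** The concern holds. The Statistical analysis section gives the pain rating, the pain 60 stimulus, the cognitive scores and, by extension, the thermal thresholds no baseline-adjusted group comparison, although their baselines are collected.

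Under the assumed correlations of 0.5 to 0.7, adjustment would cut the variance by 25% to 49% against 1-month values and by 25% to 15% against change scores. The benefit is modest against 1-month values if rho is near 0.3, and against change scores if rho is near 0.8. These figures assume equal SDs at the two visits and a linear relation with baseline.

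The sample size and the validity of the tests are unaffected. The change should be made because it improves the evidence on half of the first hypothesis and on stated secondary objectives at almost no cost.

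**What to change.** In the Statistical analysis section, extend the ANCOVA to every quantitative secondary outcome measured at both visits: the numeric pain rating, heat and cold pain thresholds, the pain 60 temperature and each Cantab score. The 1-month value is the dependent variable; group and that outcome's own baseline value are the covariates. Report the adjusted group difference with its 95% confidence interval as the result for that outcome, and keep the t-test or Mann–Whitney test as an unadjusted check. Bring the Abstract's reference to mixed models into line with the Methods.

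The cost is a sentence or two of wording, a few more regressions and one degree of freedom per model. No extra patients, visits or measurements are needed. The Trial status section reports 26 of the planned 48 patients recruited at the time of writing. Fixing the wording before unblinding also prevents a later choice between adjusted and unadjusted results.

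### The primary test is an unadjusted change-score t-test or Mann–Whitney test chosen by outcome checks; the baseline-adjusted ANCOVA is only an add-on, and the abstract names mixed models the Methods never describe

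*Protocol article*

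**What the plan says.** Four statements in the protocol article bear on the primary analysis.

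- **Conditioned pain modulation:** the endpoint comparison is on change from baseline: "The milnacipran and placebo differences (CPMv3 − CPMv1) are then compared".
- **Statistical analysis, test:** independent groups are compared by Student's t-test "or the Mann–Whitney test for quantitative parameters (notably primary outcome", and other variables), "with normality verified by the Shapiro-Wilk test and homoscedasticity by the Fisher-Snedecor test".
- **Statistical analysis, adjustment:** "the primary analysis will be completed by an analysis of covariance considering conditioned pain modulation at 1 month as a dependent variable". The explanatory terms of that model are treatment arm and baseline CPM.
- **Abstract, Methods/design:** "Data analysis is performed using mixed models; the tests are two-sided, with a type I error set at alpha = 0.05". The Statistical analysis section names no mixed model.

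The Sample size calculation follows the change-score comparison. It takes a 15-point difference, an SD of 16 for the CPM variation, 24 patients per group and 90% power, "at a two-sided alpha level of 0.05".

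**The concern.** There are three separate weaknesses.

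1. **Precision.** The primary test ignores the information in baseline CPM beyond simple subtraction. Subtraction amounts to assuming a slope of 1 between baseline and follow-up. When the correlation is below 1 and the variances are similar, the true slope is smaller, so the change score over-corrects any chance baseline difference. Such differences can easily occur with 24 per group.
2. **Test not fixed in advance.** Normality and variance checks on the outcome decide between a comparison of means and a comparison of ranks. The effect measure of the primary endpoint is therefore known only once the data are in.
3. **Inconsistent label.** A reader of the abstract expects a mixed model and a reader of the Methods finds none. The term does not settle the matter either. With two visits and complete data, the group-by-visit term of a random-intercept model reproduces the change-score t-test, whereas a version with a common baseline behaves much like ANCOVA.

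At stake are some power on the only primary question and the clarity of which estimate will be reported as the trial's result.

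**Working it through.** **Inputs from the Sample size calculation:** difference 15, SD of change 16, n = 24 per group, two-sided alpha 0.05, target power 90%.

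**Assumed:** the correlation r between baseline and 1-month CPM (not given; range 0.3 to 0.7, with 0.9 as an extreme) and equal variances at the two visits.

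**Step 1. Reproduce the plan's figure.**

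- n per group = 2 × 16² × (1.960 + 1.282)² / 15² = 23.9, so 24.
- Power at 24 per group is 90.1% by the normal approximation.
- By the non-central t (46 df), the non-centrality is 15 / (16 × √(2/24)) = 3.248 and power is 88.9%. An exact 90% would need 25 per group.

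The stated sample size is therefore not in error.

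**Step 2. Variance ratio.** Let σ be the SD at each visit.

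- Change score: variance 2σ²(1 − r).
- ANCOVA: residual variance σ²(1 − r²).
- Ratio, ANCOVA to change: (1 − r²) / [2(1 − r)] = (1 + r)/2.

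**Step 3. Power of ANCOVA with the SD of change held at 16.** The effective SD is 16 × √((1 + r)/2), with 45 df.

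| r (assumed) | Variance ratio | Effective SD | Non-centrality | Power |
|---|---|---|---|---|
| change score | 1 | 16.0 | 3.248 | 88.9% |
| 0.3 | 0.65 | 12.9 | 4.028 | 97.6% |
| 0.5 | 0.75 | 13.9 | 3.750 | 95.6% |
| 0.7 | 0.85 | 14.8 | 3.523 | 93.1% |
| 0.9 | 0.95 | 15.6 | 3.332 | 90.3% |

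The gain is about 9, 7, 4 and 1 percentage points. At r = 0.5, a change-score test would need 24 / 0.75 = 32 per group to match ANCOVA with 24.

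**Step 4. Simulation** (normal data, 24 per group, 40,000 trials per setting). At a true difference of 15, ANCOVA power was 97.4%, 95.2% and 92.6% for r = 0.3, 0.5 and 0.7. This is slightly below the formula, which ignores the small cost of estimating the slope. The change-score t-test stayed near 89%.

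| | r = 0.3 | r = 0.5 | r = 0.7 |
|---|---|---|---|
| t-test and ANCOVA disagree at 0.05, true difference 15 | 9.3% | 7.9% | 6.1% |
| Type I error if either the t-test or ANCOVA could be claimed | 7.8% | 7.1% | 6.7% |

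**Step 5. The normality switch on its own.** Using Mann–Whitney whenever Shapiro-Wilk rejects in either group, and the t-test otherwise, gave a type I error of 4.8% to 5.3% on normal data (8,000 trials per setting). The switch does not inflate error there. Its fault is that it leaves the test and the effect measure open.

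**The case against.** **The plan does state an order.** The t-test or Mann–Whitney comparison is the analysis called primary, and ANCOVA is added to it. Endpoint definition, primary test and sample size all use the change score. This stands. A reader might infer that the plan sets up several competing primary p-values and leaves the 5% error rate unprotected. The text does not support that. Picking the best of the t-test, Mann–Whitney and ANCOVA would give a type I error of about 7.4% to 8.5%, but that procedure is not in the plan: the t-test and Mann–Whitney are alternatives, and ANCOVA is not offered as a replacement. Even the 7–8% for t-test or ANCOVA arises only if the stated order is abandoned.

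**The planned test is sound.** In a randomised trial the change-score t-test is unbiased, and it has 89–90% power under the stated inputs. This also stands. It would be wrong to conclude that the trial is underpowered, or its primary test invalid, on this ground.

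**The gain depends on an unknown correlation and on equal variances.** True: at r = 0.9 little is left. Larger disagreement rates could be produced by assuming a smaller true effect, but the article's design effect is 15 points, so only the 6–9% figure rests on the plan.

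**A full analysis plan may settle the hierarchy.** It may, so the lack of a rule for discordant results is not counted here. It cannot remove the mismatch between abstract and Methods, nor the data-dependent choice of primary test, because both are stated in this article.

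**Conclusion.** The concern holds as a matter of efficiency and clarity, not of validity. The primary comparison is unadjusted, its test is chosen from the outcome data, and a more precise analysis that is already planned is given a complementary role. The abstract describes a method that the Methods do not contain.

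The cost is about 4 to 9 points of power at the design effect for r between 0.7 and 0.3, falling to about 1 point at r = 0.9. This assumes similar variances at the two visits, roughly normal data and an SD of change of 16. The sample size is reproduced, and no error inflation follows from the order as written. This change should be made, but the trial can be interpreted without it.

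**What to change.** 1. Name the ANCOVA of 1-month CPM on group and baseline CPM as the single primary analysis, and report the adjusted mean difference, its 95% confidence interval and p-value.
2. Remove the Shapiro-Wilk switch for the primary endpoint, so that the test does not depend on the outcome data.
3. Label the change-score t-test and the Mann–Whitney test as supportive.
4. Replace the abstract's reference to mixed models so that it matches the Methods.

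The cost is wording only. The model is already specified, baseline CPM is already measured at visit 1, and no extra patients or assessments are needed. The trial is double blind and the Trial status section reports 26 of the 48 patients recruited at the time of writing, so the change could be fixed and dated before unblinding.
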